**Objective 1.2:** To determine the acceptability of the bespoke Empowering Coaching training programme (Empowering Physio) to treating physiotherapists (P)	• Focus group	**Continue without modifications**: Thematic analysis identifies that intervention physiotherapists perceived that the EC training programme developed their understanding and enactment of how to create an empowering treatment climate **Stop**: Thematic analysis suggests that intervention physiotherapists perceived that the EC training programme was insufficient to develop their understanding or enactment of how to create an empowering treatment climate
**Objective 1.3**: To evaluate fidelity of intervention delivery by treating physiotherapists (S)	• Two members of the research team will assess transcripts of one intervention session from the adoption, routine formation and maintenance phases from first and third participants for the following: 1) Intervention content by coding of BCTs 2) Treatment climate using the ISPACOT [39]	• Essential pre-specified BCTs are delivered with at least mean ‘moderate’ levels of fidelity (≥ 50%) [40] • Mean score of ≥ 4/7 on Likert scale when using ISPACOT to evaluate treatment climate [41]

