#### Intervention fidelity

Fidelity assessment of delivery of the intervention will include evaluation of two aspects: what was delivered (e.g. the BCTs) and how these BCTs were delivered/overall exchanges between the physiotherapist and patient (i.e. the physiotherapy treatment motivational climate) in regard to promoting the patient’s feelings of competence, autonomy and relatedness. Physiotherapists will be asked to audio record one session from each of the adoption, routine formation and maintenance phases from their first and third participants. The specific sessions to be recorded in each intervention phase will be randomised. The audio recording will be transcribed verbatim.

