#### How was it delivered: evaluation of the treatment motivational climate

Two researchers will use the Interpersonal Support in Physical Activity Consultations Observational Tool (ISPACOT) [39], a 21-item tool that is grounded in SDT, which will be used to evaluate the treatment climate of the physiotherapy sessions. The tool assesses four aspects of the motivational climate created as follows: autonomy support, involvement, structure and interpersonal control and has demonstrated moderate to high levels of inter-rater reliability when assessments are carried out by trained users [39]. A 7-point Likert scale, ranging from 1 ‘not at all true’ to 7 ‘very true’, will be used to determine the degree of need support. The mean Likert scores will be calculated for all physiotherapists and reported for the adoption, routine formation and maintenance phases, respectively. In line with previous research, scores of ≥ 4/7 will be considered the minimum required to deliver a need supportive treatment climate [41, 79].

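### Treatment climate is to be rated with an observational tool from verbatim transcripts, although the planned audio recordings would keep the tone and manner of speech that a transcript loses

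*Protocol article*

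**What the plan says.** All references are to the protocol article.

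- **Intervention fidelity** separates what was delivered from how. The second aspect is described as "how these BCTs were delivered/overall exchanges between the physiotherapist and patient".
- The same section gives the data source: "Physiotherapists will be asked to audio record one session from each of the adoption, routine formation and maintenance phases from their first and third participants". It then adds: "The audio recording will be transcribed verbatim".
- **Trial outcomes and success criteria, Table 3, Objective 1.3** sets out the assessment: "Two members of the research team will assess transcripts of one intervention session from the adoption, routine formation and maintenance phases". Two uses of that material are listed, BCT coding and "Treatment climate using the ISPACOT". The matching success criterion is "Mean score of ≥ 4/7 on Likert scale when using ISPACOT to evaluate treatment climate".
- **What was delivered: evaluation of behaviour change techniques delivered** says that BCTs are coded from transcripts.
- **How was it delivered: evaluation of the treatment motivational climate** gives the tool's full name, "Interpersonal Support in Physical Activity Consultations Observational Tool (ISPACOT", and its scope: "The tool assesses four aspects of the motivational climate created as follows: autonomy support, involvement, structure and interpersonal control". It cites inter-rater reliability among trained users and takes the minimum score from earlier research. It does not say whether raters read, listen or watch.

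**The concern.** One source serves two measures with different needs. BCT coding asks whether a technique was present, and a verbatim text can answer that. The climate rating asks how the physiotherapist related to the patient. Warmth, pressure, pace and emphasis are carried partly by the voice, and the same sentence can be supportive or controlling depending on how it is spoken. This is a general measurement point, not a statement in the article, but it follows from the article's own division between what and how.

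An empowering treatment climate is the overarching aim of the intervention and the focus of the physiotherapist training. The ISPACOT mean is the only criterion in Table 3 by which someone other than the patient or the physiotherapist judges whether that climate was created. If raters see only the wording, this check becomes weaker. Agreement between the two raters would not reveal the problem, because two readers can agree well on a text from which the relevant information is missing.

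**Working it through.** There is no stated figure to reproduce, and no sample size or power calculation bears on the point. The check sets the sections side by side, then counts recordings and listening time.

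**1. Source named for each measure**

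| Place | BCT coding | ISPACOT rating |
|---|---|---|
| Table 3, Objective 1.3 | transcripts | transcripts |
| Intervention fidelity | audio, then transcribed | audio, then transcribed |
| Section on what was delivered | transcripts | not covered |
| Section on how it was delivered | not covered | no source named; refers only to the sessions |

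Table 3 is therefore the only place that names the material for the ISPACOT rating, and it names transcripts. Nowhere does the article say that raters listen to the recordings.

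**2. Support for rating from text.** The climate section gives reliability for trained users and a minimum score from earlier research. For neither does it say whether the underlying ratings were made live, from audio or from text.

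**3. What audio would add.** Sessions may be in person, by phone or by video (Intervention delivery). In a phone session the voice is the whole interpersonal channel: audio keeps it and a transcript does not. In the other two formats audio still misses non-verbal behaviour, but it holds more than the text.

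**4. Recordings already planned.** The abstract gives 5–6 physiotherapists; the sections on focus groups and physiotherapist training give 6–7. Recordings = physiotherapists × 2 participants × 3 phases:

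- 5 × 2 × 3 = 30
- 6 × 2 × 3 = 36
- 7 × 2 × 3 = 42

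**5. Listening time per rater.** Intervention delivery gives 45 min for an initial appointment and 30 min for a follow-up. Each participant has one initial appointment, so at most one of that participant's three recordings can last 45 min.

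- Lower end: 30 sessions, all follow-ups: 30 × 0.5 h = 15 h.
- Upper end: 42 sessions from 14 participants, each with the initial session recorded: 14 × 0.75 h + 28 × 0.5 h = 10.5 h + 14 h = 24.5 h.

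**6. Size of any bias.** If k of the 21 items were each misjudged by one point in the same direction, a session mean would shift by k/21. The article gives no basis for k, for the size of the error or for a common direction, and errors in both directions could cancel. No figure is claimed.

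**The case against.** The strongest case on the other side has four parts.

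- **Table 3 may be shorthand.** One table cell summarises two measures in a condensed article. The section that governs the ISPACOT speaks of sessions, not transcripts, and raters may in practice have the audio. A reader might infer that the recordings are discarded for this measure; the article does not say so. What stands is that the only stated source is the transcript. If practice differs, Table 3 needs the same edit.
- **Unsuitability is not proven.** The 21 items and the tool's validation are not shown. Autonomy support and structure may rest largely on wording, and a verbatim transcript can mark pauses and interruptions. The medium behind the cited reliability is unstated in either direction. This stands, and it limits the point to lost information of unknown consequence.
- **Other evidence on climate exists.** Table 4 includes the patient-reported Health Care Climate Questionnaire at 3 months, and Objective 1.2, a primary outcome, asks physiotherapists about their enactment of an empowering climate. So the trial does not rely on the ISPACOT alone. Neither source is observer-rated, however, and the questionnaire has no threshold in Table 3.
- **The stakes are modest.** Objective 1.3 is marked secondary, and the Table 3 legend ties only primary outcomes to progression. It has no Stop threshold. This stands in full.

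**Conclusion.** The point holds as a low-cost improvement to a secondary outcome. Followed as written, the plan rates the manner of delivery from text that loses part of that manner, while a fuller record of the same sessions is already planned. The conclusion rests on Table 3 meaning what it says and on the general premise that voice carries information about involvement and interpersonal control.

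Two stronger readings are tempting and are not supported. A reader might infer that a result at the 4 out of 7 cut-off would be wrong by a known amount, or that progression to the definitive trial depends on it. The documents allow no estimate of bias, and the criterion is not tied to progression. A reader might also infer that transcripts prevent the trial from showing whether training changed how physiotherapists behave. With a single arm and no pre-training recordings described, audio ratings could not show that either.

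**What to change.** In Table 3 (Objective 1.3) and in the section on the treatment motivational climate, state that the two researchers make the ISPACOT ratings from the audio recordings, with the transcript as an aid. Keep transcripts alone for BCT coding. If there is evidence that the tool and its cut-off are valid when applied to transcripts, citing it would be an acceptable alternative.

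The change is one of wording. It needs no new recordings or staff and adds no burden for patients. The cost is about 15 to 24.5 hours of listening per rater, partly replacing time spent reading, and the recordings must be kept until rating is complete.

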#### What was delivered: evaluation of behaviour change techniques delivered

Two members of the research team will code all transcripts to identify the BCTs delivered. A coding manual will be provided to coders to optimise consistency. It will include intervention BCTs definition as per the V1 taxonomy [76] and examples of how the technique may be delivered or described in the intervention. BCTs will only be coded once per session and will be written as either (1) fully delivered or (2) partially delivered [77]. BCTs that were present but not part of the specific protocol will also be noted [78]. Coders will have completed online training for BCT identification using the V1 taxonomy and have experience coding BCTs from intervention manuscripts [12] and transcribed interviews with high levels of reliability. The median and interquartile range of BCTs per session in the adoption, routine formation and maintenance phases will be reported respectively. The number of times each BCT was fully delivered compared to when it was outlined in the treatment manual will be averaged across physiotherapists and calculated as a percentage. Overall fidelity will be categorised as *high* if ≥ 80% of essential BCTs are present, *moderate* if 50–79% are present, and *low*if 0–49% are present [40, 78].

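### The BCT fidelity criterion in Objective 1.3 is one pooled mean of at least 50% with no floor per phase, so it can be met when the maintenance phase is wholly undelivered

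*Protocol article*

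**What the plan says.** Table 3 (Objective 1.3, marked as a secondary outcome) gives two success criteria for fidelity. For content: "Essential pre-specified BCTs are delivered with at least mean ‘moderate’ levels of fidelity (≥ 50" per cent). For treatment climate: "Mean score of ≥ 4/7 on Likert scale when using ISPACOT to evaluate treatment climate".

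The Methods explain how the content figure is built. In the section on what was delivered, "The number of times each BCT was fully delivered compared to when it was outlined in the treatment manual will be averaged across physiotherapists" and expressed as a percentage. Overall fidelity is then "categorised as *high* if ≥ 80% of essential BCTs are present, *moderate* if 50–79% are present", and low below that. The same section adds a description by phase: "The median and interquartile range of BCTs per session in the adoption, routine formation and maintenance phases will be reported respectively". No pass mark is attached to it.

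Sampling is by phase. Under Intervention fidelity, physiotherapists are asked to "audio record one session from each of the adoption, routine formation and maintenance phases from their first and third participants". For climate, the section on how the intervention was delivered says: "The mean Likert scores will be calculated for all physiotherapists and reported for the adoption, routine formation and maintenance phases, respectively". It then gives 4 out of 7 as the minimum for a need-supportive climate.

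**The concern.** The Background describes the clinical problem as benefit that fades by about 6 months because patients do not keep up their activity. It gives adoption and maintenance as the joint targets of the techniques. The design follows this, with separate materials for the later sessions and a separate recording in each phase. The content criterion does not use that structure. A mean over all essential techniques lets good delivery early on offset absent delivery later.

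Objective 1.3 is the plan's only observed measure of what the physiotherapists deliver; Objectives 1.1 and 1.2 rest on interviews and focus groups. If it can report at least moderate fidelity when a whole phase is missing, the team designing the definitive trial could believe that the three-phase intervention had been delivered when it had not.

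**Working it through.** The 50% mark is a chosen cut-off, so there is no derived figure to reproduce. The check asks which delivery patterns meet it.

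**Inputs**

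- Table 2, sessions 1–2: workbook 5 BCTs, pedometer 2 (self-monitoring repeated, so 1 new), information book 3. Distinct: 5 + 1 + 3 = 9; row entries: 5 + 2 + 3 = 10.
- Table 2, sessions 3–4: 5 BCTs (problem-solving repeated, so 4 new).
- Table 2, any session: 3 BCTs (habit formation repeated, so 2 new).
- Essential BCTs, and how often the manual schedules each: not in the article. Assumption: the Table 2 BCTs are the essential set. Several counts are shown because the denominator is unknown.
- Recordings per phase: 2 participants per physiotherapist. The article gives 5–6 physiotherapists in the Abstract and 6–7 in the Methods, so 5 × 2 = 10 to 7 × 2 = 14.

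**Formula**

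Pooled fidelity F = w_a·f_a + w_r·f_r + w_m·f_m. Here w is the share of essential BCT occasions due in adoption, routine formation and maintenance, and f is the proportion delivered. The criterion is met if F ≥ 50%.

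**Step 1. Only maintenance undelivered (f = 100%, 100%, 0%)**

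F = 1 − w_m, so the criterion is met whenever maintenance carries no more than half of the weight.

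- Equal phase weights: (100 + 100 + 0)/3 = 67%. Pass.
- Sessions 3–4 BCTs due in both later recordings (9 + 5 + 5 = 19): 14/19 = 74%. Pass.
- As above, but with half of the adoption BCTs due in the one recorded adoption session (assumed split): (4.5 + 5)/14.5 = 66%. Pass.

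Delivery in the other phases need not be perfect. With equal weights, (75 + 75 + 0)/3 = 50% and (100 + 50 + 0)/3 = 50% both just pass.

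**Step 2. Both later phases undelivered (f = 100%, 0%, 0%)**

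F = w_a, and the answer depends on the count.

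| Count | F | Result |
|---|---|---|
| Distinct BCTs, sessions 1–4, problem-solving credited to adoption | 9/13 = 69% | pass |
| Row entries, sessions 1–4 | 10/15 = 67% | pass |
| BCTs counted once per block | 9/14 = 64% | pass |
| Distinct, with any-session BCTs undelivered | 9/15 = 60% | pass |
| Row entries, with any-session BCTs undelivered | 10/18 = 56% | pass |
| Distinct, any-session undelivered, problem-solving not credited | 8/15 = 53% | pass |
| Per block, with any-session BCTs undelivered | 9/17 = 53% | pass |
| Sessions 3–4 BCTs due in both later recordings | 9/19 = 47% | fail |
| Half of the adoption BCTs due in the recorded session (assumed), later BCTs counted once | 4.5/9.5 = 47% | fail |
| Equal phase weights | 1/3 = 33% | fail |

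**Step 3. The same mark applied within each phase**

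In Step 1 maintenance scores 0% and fails. In Step 2 both later phases score 0% and fail. The result no longer depends on how many BCTs each phase contributes.

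**ISPACOT**

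If Table 3 means one overall score, illustrative phase means of 5.5, 4.5 and 2.0 give 12.0/3 = 4.0 and pass. If 4 out of 7 applies to each phase mean, the third phase fails. Table 3 does not say which is meant.

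**The case against.** The strongest reply is that the article gives neither the essential list nor the manual's schedule. The true denominator is therefore unknown, and Table 2 names are only a stand-in. That stands, and it limits what can be claimed. A reader might infer that the intervention passes even if no routine-formation or maintenance technique is delivered. The documents do not support this as a general statement: Step 2 gives passes and fails depending on the count. The reply does not reach Step 1, where any pooling passes so long as maintenance carries at most half of the weight.

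Second, the criterion could be read technique by technique. The Methods compute a percentage for each BCT and average across physiotherapists, so an essential BCT that was never delivered would score 0% and fail. The wording leaves room for this, but the bands classify overall fidelity by the share "of essential BCTs are present", which favours the pooled reading. If the per-BCT reading is intended, Table 3 needs to say so.

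Third, the ISPACOT paragraph already reports means by phase and states the 4 out of 7 minimum straight afterwards, so that minimum plausibly applies to each phase. This largely stands; for ISPACOT the issue is only that Table 3 does not match the Methods. ISPACOT cannot stand in for the content criterion, because it rates climate, not which techniques were given.

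Fourth, a reader might infer that a definitive trial would follow on a component never delivered. That goes too far. The Table 3 legend ties only primary outcomes to progression, Objective 1.3 has no stop or continue bands, BCT counts per session are reported by phase, and the Trial Steering Group considers modifications with patient and public involvement. The section on success criteria does say that each criterion is evaluated in deciding whether to recommend progression, so the result still informs the decision.

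Last, three thresholds in place of one rest on fewer transcripts each and raise the chance of failing an intervention that was adequately delivered. That is a real cost of the change.

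**Conclusion.** The concern holds in a limited form. On the pooled reading, which the overall fidelity wording favours, the content criterion has no phase floor and can be met with the maintenance phase wholly undelivered: 67% with equal phase weights, 74% on Table 2 counts with the sessions 3–4 techniques due in both later recordings. This needs only that maintenance carry no more than half of the weight and that delivery in the other phases be high enough.

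A pass with nothing delivered in either later phase is possible but not established. It gives 53–69% on several Table 2 counts and 47% or 33% on others, all taking Table 2 as the essential set and adoption as fully delivered.

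The consequence is a fidelity result that could be labelled a success while a phase central to the intervention's purpose was missing. The phase-level counts should make this visible, but they would not change the label. This is worth correcting because the change is small and the data are already planned.

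**What to change.** In Table 3, Objective 1.3, state that the essential BCTs due in each of the adoption, routine-formation and maintenance phases must reach mean fidelity of at least 50% in that phase. Keep the pooled percentage and its high, moderate and low bands as description only, and make the matching change in the section on what was delivered. State in Table 3 whether the ISPACOT minimum of 4 out of 7 applies to each phase mean, consistent with the section on how the intervention was delivered.

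The cost is wording. No extra recordings or coding are needed, because sessions are already sampled by phase. The criterion becomes somewhat stricter, each phase estimate rests on about 10–14 transcripts, and a phase mean of 50% can still hide an individual technique that was never delivered. The per-BCT percentages already planned should therefore be read alongside it.

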**Aim 2: Trial feasibility and acceptability**		
**Objective**	**Method of assessment**	**Success criteria**
**Objective 2.1**: To measure the recruitment rates of participants (P)	• Recording number (*n*) of participants who were sent a participant information sheet, number who agreed to participate and number recruited per month	**Continue without modification** • Target of *n* = 35 participants recruited in 9 months (approx. 4/month) • Conversion rate of ≥ 30% (number sent PIS/ number who agreed to participate) **Stop** • Target of *n* = 35 participants recruited takes > 12 months (less than 3/month) • Conversion rate of ≤ 15% (number sent PIS/ number who agreed to participate)
**Objective 2.2**: To measure the completeness of data collection of performance-based and patient-reported outcome measures at baseline, 3- and 6-month post-baseline (P)	• Record number of PROMs returned to trial team and number of participants who completed performance-based outcomes during virtual outcome assessments at each timepoint	**Continue without modification** • ≤ 80% PROM and performance-based data collected at 3-month post-baseline • ≤ 70% PROM and performance-based data collected at 6-month post-baseline **Stop** • ≤ 50% PROM and performance-based data collected at 3-month post-baseline • ≤ 50% PROM and performance-based data collected at 6-month post-baseline
**Objective 2.3**: To determine the feasibility and acceptability of trial-related procedures (recruitment, outcome assessment) to participants and ROH research staff ((P)	• Participants: Semi-structured interviews • ROH research staff: Focus groups	**Continue with modification** • Thematic analysis identifies that trial participants and ROH research staff are satisfied (i.e. feasible and acceptable) with trial procedures (e.g. recruitment, outcome assessment) in semi-structured interviews and focus groups respectively **Stop** • Thematic analysis identifies that trial participants and ROH research staff are not satisfied (i.e. they do not perceive it is feasible and/or acceptable) with trial procedures (e.g. recruitment, outcome assessment) in semi-structured interviews and focus groups respectively
**Objective 2.4**: To determine the feasibility and acceptability of utilising an accelerometer as the primary outcome in a definitive randomised controlled trial (S)	• % of accelerometers returned to research staff with valid data • Semi-structured interviews	• ≤ 70% of accelerometer data collected at 6-month post-baseline • Accelerometer data will be considered valid if it has been recorded for ≥ 10 h [42, 43] for ≥ 4/7 days, with at least one falling on a weekend [44–46] • Participants state that they believe that accelerometer is feasible and acceptable to use as the primary outcome measure in future definitive trial
**Objective 2.5**: To determine the acceptability of the patient-reported and performance-based outcome measures to participants ((S)	• Semi-structured interviews	• Participants report that they found the patient-reported and performance-based outcomes feasible and acceptable, and the time taken to complete was satisfactory for use in a definitive randomised controlled trial

Legend: *ISPACOT* Interpersonal support in physical activity consultations observational, *P* Primary feasibility outcome related to progression to definitive trial, *S* Secondary feasibility outcome

Once it has been established if each criterion has been met, further consultation with patient and public involvement (PPI) at Trial Steering Group meetings will be utilised to determine if and what modifications the intervention requires to progress to the full-scale RCT (e.g. adaptions to intervention to enable delivery in alternative NHS physiotherapy departments).

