### Participant identification and consent

#### Feasibility trial

Potential participants will be identified from the physiotherapy waiting lists at the ROH by a member of the research team. If the patient appears to meet the eligibility criteria, they will be sent a participant information sheet (PIS) and trial consent form via post. Each potential participant will be phoned by a research nurse a minimum of 1 week later. Potential participants will be asked if they have reviewed the PIS and if they are interested in trial participation. If they report being interested, the research nurse will confirm eligibility, outline the trial and answer any outstanding questions. Consent will be taken by the research nurse during the phone call and witnessed by another ROH staff member. During the meeting, the research nurse will reiterate that participants are free to withdraw from the trial at any time, and that this will not impact on their current or future healthcare [31].

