#### Sample size

Although a formal calculation was not completed, total sample sizes of between *n* = 24 to 50 are recommended in feasibility trials and a sample of 30 [18] to 35 [75] considered sufficient to ensure normal distribution of participants. An audit of the ROH physiotherapy waiting lists suggested that approximately 65 patients with musculoskeletal pain are referred to the ROH each week, and that approximately 5% would be eligible to participate in the trial (i.e. three per week). Based on previous trials conducted at the ROH, approximately one in three of those approached consents to participate. Therefore, based on trial resources and timelines, recruitment of a target sample of up to 35 participants over a 9-month period is estimated.

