### Data analysis

#### Quantitative

The primary quantitative data analysis will be descriptive [19, 31]. A CONSORT diagram will outline the number of participants who were identified, recruited, commenced and finished treatment, and the recruitment rate (number/month and number approached/number recruited) will be reported as a percentage [29]. Where possible, reasons for refusal and dropout during the intervention will be recorded and reported. A Shapiro–Wilk test will test the normality of continuous data (e.g. PROM and accelerometer data), and the mean and 95% confidence intervals will be reported for each. The number of non-completed/partially completed PROMs, performance measures and accelerometer data at each timepoint will be expressed as a percentage. Partially completed PROM and accelerometer data will not be included in the data analysis, but potential reasons, including practicality, will be discussed in the interviews.

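### The conversion rate in Objective 2.1 is defined upside down, so its continue threshold (≥ 30%) is always met and its stop threshold (≤ 15%) can never be reached

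*Protocol article*

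**What the plan says.** Objective 2.1 in Table 3 of the protocol article is marked P, which the table legend defines as a primary feasibility outcome tied to progression to the definitive trial. The data to be recorded are the number of "participants who were sent a participant information sheet, number who agreed to participate and number recruited per month". Each decision has two parts.

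- **Continue without modification:** "Target of *n* = 35 participants recruited in 9 months (approx. 4/month"), and "Conversion rate of ≥ 30% (number sent PIS/ number who agreed to participate").
- **Stop:** reaching 35 takes more than 12 months, and "Conversion rate of ≤ 15% (number sent PIS/ number who agreed to participate").

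Three other places bear on this.

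- **Participant identification and consent, Feasibility trial:** if patients on the waiting list appear eligible, "they will be sent a participant information sheet (PIS) and trial consent form via post". The telephone call and consent come afterwards.
- **Sample size:** "approximately 5% would be eligible to participate in the trial (i.e. three per week"), and "approximately one in three of those approached consents to participate".
- **Data analysis, Quantitative:** the recruitment rate, given as "number/month and number approached/number recruited", is to be reported as a percentage.

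**The concern.** A conversion rate is the share of those invited who take part. The protocol prints the reciprocal. Its numerator is the larger group and its denominator is a subset of that group, so the ratio has a floor of 100%, while both thresholds lie far below that floor. The planning assumption of one in three is stated in the opposite direction, so the protocol contradicts itself.

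The section on trial outcomes and success criteria says that the trial's success will be judged against these criteria, fixed in advance. If one of them cannot fail, it carries no information. Anyone who notices after the data are in must change the formula of a primary progression rule with the result already known.

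**Working it through.** **Inputs**

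- Continue at ≥ 30%, stop at ≤ 15%, printed formula sent/agreed (Table 3, Objective 2.1).
- Target of 35 in 9 months; stop if more than 12 months (same place).
- About 65 referrals per week, 5% eligible, stated as three per week; about one in three of those approached consents (Sample size).
- The information sheet is sent before consent (Participant identification and consent), so agreed ≤ sent.

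**Step 1. Reproduce the plan's own recruitment figures.** 35/9 = 3.9 per month, stated as about 4. 35/12 = 2.9, stated as less than 3. Eligible patients: 65 × 0.05 = 3.25 per week, stated as three. Taking 9 months as 36 to 39 weeks:

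- low end: 3 × 36 × 1/3 = 36 recruits;
- high end: 3.25 × 39 × 1/3 = 42 recruits.

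Both are consistent with a target of up to 35. This works only if the one in three is consented divided by approached.

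**Step 2. Range of the printed ratio.** Since 1 ≤ agreed ≤ sent, sent/agreed ≥ 1, that is ≥ 100%. Equality holds only if everyone sent the sheet agrees. If nobody agrees the ratio is undefined, and the stop criterion is still not met.

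**Step 3. Both directions at a range of true uptakes.** The printed ratio is 1 divided by the uptake.

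| Agreed/sent | Printed sent/agreed | Verdict as printed | Verdict with agreed/sent |
|---|---|---|---|
| 100% | 100% | continue | continue |
| 33% | 300% | continue | continue |
| 30% | 333% | continue | continue |
| 20% | 500% | continue | between the limits |
| 15% | 667% | continue | stop |
| 5% | 2000% | continue | stop |

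The printed column never falls below 30% and never reaches 15%. The band between the two limits is unreachable as well, and the scale runs backwards.

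**Step 4. Check that the thresholds work the other way up.** Take 35 people agreeing, for illustration.

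- Continue needs 35/sent ≥ 0.30, so sent ≤ 35/0.30 = 116.7: at most 116 sheets (35/116 = 30.2%; 35/117 = 29.9% just misses).
- Stop needs 35/sent ≤ 0.15, so sent ≥ 35/0.15 = 233.3: at least 234 sheets (35/234 = 14.96%; 35/233 = 15.02% just misses).

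Both limits are reachable, and the expected 33% sits just above the continue line, as one would design it.

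**Step 5. What the time criterion covers alone.** At the planned three eligible patients per week, 52 weeks give 156 invitations. At 15% uptake that yields 156 × 0.15 = 23 recruits, so the time rule would also call a stop. If more patients can be invited than planned, it would not: 234 invitations over 39 weeks is 234/39 = 6 per week, and 35 would be recruited within 9 months at 15% uptake. In that case only the conversion rate would show the poor uptake.

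**The case against.** The strongest reply is that nobody would be misled. The term itself, the size of the thresholds and the one-in-three assumption all point to agreed/sent, and an analyst who obtained 300% at the planned uptake would see the reversal at once. It is a notation error with one evident correction. Recruitment also has the time criterion, which is correctly stated and, at the planned inflow, would catch very low uptake by itself. The two Table 3 cells repeat one phrase, and the Quantitative section describes a reported figure with no threshold attached, so the inversion there disables no decision.

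Much of this stands. The intended direction can be inferred, the damage is confined to the conversion part of Objective 2.1, and a careful team would probably compute the right quantity. The objection does not make the text right, however. Table 3 states the numerator and denominator explicitly, and the Quantitative section says its similarly ordered ratio is reported as a percentage, so the slash cannot be read there as merely listing two counts. A stop rule fixed in advance should not depend on readers silently reversing it. The time rule also measures something else: it tracks speed, which depends on how many are invited, and the conversion rate tracks willingness.

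**Conclusion.** The concern holds. As written, the conversion-rate component of a primary progression outcome is met at any non-zero uptake and its stop rule cannot fire. The printed value is 300% at the planned uptake, 667% at the intended stop limit and 2000% at 5% uptake, against limits of 30% and 15%.

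The conclusion rests on one assumption, which the consent procedure supports: everyone who agrees was first sent the information sheet. It does not depend on the use of 35 as the number agreeing, which serves only to express the limits as counts. The time component of Objective 2.1 is unaffected. The error should be corrected before the criteria are applied.

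**What to change.** Reverse the ratio in three places.

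1. Table 3, Objective 2.1, continue cell: number who agreed to participate divided by number sent the information sheet, ≥ 30%.
2. Table 3, Objective 2.1, stop cell: the same ratio, ≤ 15%.
3. Data analysis, Quantitative: number recruited divided by number approached, as a percentage.

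The thresholds need no change, and the counts required are already being recorded. The cost is a wording correction, with no effect on sample size, conduct or data collection. Reporting the rate with a 95% confidence interval would help the reader but is optional and separate from the error.
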